***Biochemical***

The table below indicates the cut-off points that will be used to compare normal values of pre-school children (IZiNCG, 2007) and iron.

**Table 3.2: An indication of lower cut-offs for serum zinc concentration (μmol/dL) by age group, gender, time of day and time since last meal** (IZiNCG, 2007).

| **Time of Day and Fasting Status** | **<10 years** | **≥10 years** | |
| --- | --- | --- | --- |
|  | **Males and Females** | **Non-pregnant females** | **Males** |
| Morning (fasting) | Not available | 70 μg/dL | 74 μg/dL |
| Morning (non-fasting) | 65 μg/dL | 66 μg/dL | 70 μg/dL |
| Afternoon (non-fasting) | 57 μg/dL | 59 μg/dL | 61 μg/dL |

***For conversion to μmol/L, divide by 6.54***

**Interpretation of Iron indicators**

***Table 3.3: An indication of lower cut-offs of serum iron concentration (*μg/L) by age**

| Anaemia | Hb levels <11 g/dL |
| --- | --- |
| Moderate anaemia | Hb level between 7 to 9.9 g/dL |
| Mild anaemia | Hb >10 to <11 g/dL |
|  | Hb<7 g/dL |
| Serum ferritin | (SF) <12 μg/L |
| Transferrin saturation | TSAT <15%. |
| C-reactive protein | 1 and 2.9 mg/L |

*de Benoist B, McLean E, Egli I, Cogswell M, editors. Worldwide prevalence of anaemia 1993–2005: WHO global database on anaemia accessed 20/01/ 2018*

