Despite the legislated fortification of staple foods in South Africa since 2003, micronutrient deficiencies persist. Nutritional deficiencies during childhood have resulted from a sustained negative balance of iron. This imbalance may be caused by inadequate dietary intake, absorption and/or utilization of iron, increased iron requirements during the growth period, or blood loss due to parasitic infections such as hookworm and malaria. According to SANHANES-1 (2013), the prevalence of anaemia in children less than five years of age was 10.7%; mild anaemia, 8.6%; and moderate anaemia 2.1%. However, no cases of severe anaemia have been reported. When comparing the results of SANHANES-1 with those of the 2005 NFCS, the prevalence of anaemia decreased by 63%, that of iron deficiency anaemia by 83.2%. and that of iron deficiency increased by 3.8%

The co-existence of iron and zinc deficiency is a major public health problem ([Cole](https://www.ncbi.nlm.nih.gov/pubmed/?term=Cole%20CR%5BAuthor%5D&cauthor=true&cauthor_uid=20147474) *et al*., 2010; Liu *et al*., 2011). These micronutrients are essential for human health. Deficiencies of these two trace elements remain a global problem, especially among women and children in developing countries (Antunes *et al*., 2010). However, it seems that dietary zinc reduces iron biochemical indices, including ferritin, haemoglobin (Hb) and transferrin saturation ([name] *et al*., 2015). In addition, these deficiencies may be associated with infections and parasitic infestations (Setnick, 2010; Amare *et al*., 2012). The consequences of a combined two-micronutrient insufficiency may be growth faltering (Cole *et al.,* 2010; Alves *et al*., 2012), delayed development (Baumgartner *et al.,* 2013) and increased morbidity due to infectious disease (Harrison, 2010; Shaw and Friedman, 2011). All of these can dramatically affect the health, development and well-being of the child. Pre-school children will be the focus of this research, as this age is an important stage of life in which nutrition plays an important role and has long lasting effects in later life (Khan Khattak and Ali, 2010).

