According to SANHANES-1 (2013), the prevalence of anaemia in children was 10.5% while iron deficiency was 11% and iron deficiency anaemia was 2.1%. In South Africa, the prevalence of anaemia in children less than five years of age has decreased by approximately *14*% since 2005 (Shisana *et al*., 2013). The prevalence of anaemia (hemoglobin < 11 g/dl) was lower in the SANHANES-1 survey in children under five years of age, as compared to NFCS of 2005 and the SAVACG survey, at 10.7%, 28.9% and 21.4%, respectively (Shisana *et al*., 2013). In the Capricorn District, Limpopo province, Mamabolo and Alberts (2014) reported that the prevalence of anaemia has dropped to 23.6% and the iron deficiency increased to 52.8% at one year of age when compared to 2005 NFCS. In the Vhembe District, Limpopo province [name] *et al*. (2015) found that 28% of preschool children were anaemic. In addition, the prevalence of iron deficiency was 7.2% when using serum ferritin and even higher (28.1%) when with transferrin saturation as the indicator of iron status.

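### Table 3.3 (iron indicators) gives no anaemia grade to a haemoglobin of 10.0 g/dL, so the grade counts can fall short of total anaemia

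*Protocol*

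**What the plan says.** The Biochemical part of the baseline data analysis introduces its reference tables with "The table below indicates the cut-off points that will be used to compare normal values of pre-school children". Table 3.3 on iron indicators follows. (A later table, the feeding-trial schematic, carries the same number and is not meant here.) Its haemoglobin rows are:

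- anaemia: "Hb levels <11 g/dL"
- moderate anaemia: "Hb level between 7 to 9.9 g/dL"
- mild anaemia: "Hb >10 to <11 g/dL"
- a row below 7 g/dL, whose label is blank in the text at hand.

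The overall limit is repeated in section 1.5.1: "The prevalence of anaemia (hemoglobin < 11 g/dl) was lower in the SANHANES-1 survey". No other section gives limits for the grades. Section 3.6.4.4 applies the baseline analysis procedures again after the feeding trial, so the same table serves both surveys.

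**The concern.** The moderate row stops at 9.9 and the mild row begins strictly above 10. A result of 10.0 lies between them, although it is clearly below the anaemia limit of 11. An analyst who codes the table as written obtains anaemic children without a grade. Those children must then be left out of the grade frequencies, or be given a grade by a choice made after the data are in. In the first case mild, moderate and below 7 do not add up to total anaemia. In the second, a classification rule that the protocol appears to have fixed is in fact set at analysis.

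**Working it through.** **Inputs from the protocol**

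- Anaemia below 11; moderate 7 to 9.9, read as including both ends; mild above 10 and below 11; lowest row below 7 (all g/dL, Table 3.3).
- Anaemia prevalence, for the illustration of size: 10.7% in under-fives nationally (sections 1.1 and 1.5.1) and 28% in the district (section 1.5.1: "found that 28% of preschool children were anaemic").
- Planned number of children: 436 (section 3.4), which is 396 plus a 10% attrition allowance.

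**Assumptions, not in the protocol**

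- Haemoglobin is normally distributed with an SD of 0.9 to 1.3 g/dL and is reported to 0.1 g/dL.

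**Step 1: apply the rows as written**

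| Hb (g/dL) | Below 11? | Below 7? | 7 to 9.9? | Above 10, below 11? | Grade |
| --- | --- | --- | --- | --- | --- |
| 9.9 | yes | no | yes | no | moderate |
| 10.0 | yes | no | no | no | none |
| 10.1 | yes | no | no | yes | mild |

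**Step 2: check every value below 11**

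In steps of 0.1 g/dL from 0.0 to 10.9 there are 110 values. The row below 7 takes 70, moderate takes 30 and mild takes 9, and 70 + 30 + 9 = 109. The one left over is 10.0, and no value falls in two rows. In steps of 0.01 g/dL the ungraded values are 9.91 to 10.00.

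**Step 3: illustrate the size**

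With one-decimal reporting, a reported value below 11.0 means an underlying value below 10.95, and a reported 10.0 means an underlying value from 9.95 to 10.05. For prevalence p and standard deviation SD:

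- mean = 10.95 − SD × z(p), where z(0.107) = −1.243 and z(0.28) = −0.583
- share at 10.0 = Φ((10.05 − mean)/SD) − Φ((9.95 − mean)/SD)

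Example with p = 0.28 and SD = 0.9: the mean is 10.95 + 0.9 × 0.583 = 11.475. The share is Φ(−1.583) − Φ(−1.694) = 0.0567 − 0.0451 = 0.0116, and 436 × 0.0116 = 5.1 children.

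| p | SD | Mean | Share at 10.0 | Of 436 | Share of the anaemic |
| --- | --- | --- | --- | --- | --- |
| 10.7% | 0.9 | 12.07 | 0.32% | 1.4 | 3.0% |
| 10.7% | 1.1 | 12.32 | 0.40% | 1.7 | 3.7% |
| 10.7% | 1.3 | 12.57 | 0.44% | 1.9 | 4.1% |
| 28% | 0.9 | 11.48 | 1.16% | 5.1 | 4.1% |
| 28% | 1.1 | 11.59 | 1.27% | 5.6 | 4.6% |
| 28% | 1.3 | 11.71 | 1.30% | 5.7 | 4.6% |

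If attrition brings the post-trial survey down to 396, the same shares give 1.3 to 1.7 children at 10.7% and 4.6 to 5.1 at 28%.

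**Step 4: confirm that a shared boundary closes the gap**

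If the upper end of moderate and the lower end of mild are the same number, and that number is assigned to one grade only, every value below 11 falls in exactly one row in both the 0.1 and the 0.01 grid.

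**The case against.** The strongest reply is that this is a slip in one descriptive table, which any analyst would notice and settle when coding the categories. Table 3.5 lists haemoglobin without mentioning grades, section 3.6.4.4 measures change by regression and ANOVA, and the hypothesis concerns zinc and iron status. This stands as a limit on the importance of the point. It does not remove it, because the protocol presents these limits as the ones to be used and nothing else in it places 10.0.

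Three stronger readings are tempting, and the document does not support them.

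- A reader might infer that the gap creates false movements between grades from baseline to the post-trial survey. No analysis of grade transitions is planned.
- A reader might infer that mild anaemia in particular is undercounted. That presumes 10.0 belongs to mild. If it belongs to moderate, moderate is undercounted instead, and the protocol does not settle which.
- A reader might take the national survey figures in section 1.1 ("the prevalence of anaemia in children less than five years of age was 10.7%; mild anaemia, 8.6%; and moderate anaemia 2.1" percent, where 8.6 + 2.1 = 10.7) as proof that the trial means its own grades to add up. That passage summarises literature. It shows grades that do sum to the total, which is the sensible expectation, but it neither describes how this trial grades children nor names the survey as its comparator.

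The gap is also unlikely to come from the conversion of the PDF. Both limits are legible in intact rows, and the blank label on the row below 7 plays no part.

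**Conclusion.** Wrong as written, minor. The existence of the gap needs no assumption beyond reading the moderate row as including 9.9; if that end were excluded, the gap would be wider. At two decimals it covers every value above 9.9 up to and including 10.0. At each survey the grade frequencies fall short of total anaemia by the number of children in the gap, and the grade that should hold them is undercounted by that number.

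The estimate of about 1 to 2 of 436 children at 10.7% anaemia, and about 5 to 6 at 28%, rests on the assumed normal shape, the assumed SD and one-decimal reporting. The 28% is itself an uncertain input, because the protocol calls it anaemia in section 1.5.1, iron deficiency anaemia in section 2 and iron prevalence in section 3.3. Only the descriptive grade frequencies are affected. Total anaemia prevalence and continuous haemoglobin do not depend on the grade limits.

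**What to change.** Reconcile the mild and moderate rows of Table 3.3 so that they meet at a single shared boundary, with one row including it and the other excluding it. Every haemoglobin below 11 g/dL then falls in exactly one grade at any reporting precision. The investigators should take from the source cited under the table which grade holds 10.0. Changing only the sign in the mild row so that it includes 10 would close the gap for results reported to 0.1 g/dL but would leave 9.91 to 9.99 ungraded at two decimals, and the protocol does not state the reporting precision. Add one check to the analysis: at each survey, the grades must sum to the number of children below 11 g/dL. The cost is a small edit to one table and one line of checking, with no effect on data collection or sample size.

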3.6.2.2.2. To measure the anthropometry of the study participants (Weight, Height, MUAC)

3.6.2.2.3. Determine the dietary diversity scores of participants using 24- hour recall

- - - - 1. Determine dietary patterns of the study participants using FFQ.
        2. To determine serum zinc concentrations among pre-school children using flame atomic absorption spectrophotometer before consuming *Cucurbita moschata* seeds.
        3. To determine the iron status of pre-school children using hemoglobin, serum ferritin, transferrin receptor and C- reactive protein (CRP) before consuming the *Cucurbita moschata* (butternut) seeds.

**3.6.2.3. Design:** The study design will be a cross sectional survey in which the researcher will measure the demographic and environmental factors, anthropometries, diet patterns, zinc and iron status of pre-school children. A cross sectional study is a method that involve observation of a population or a representative subset at one specific point in time (Leedy and Ormrod, 2010). All measurements parameters will be done at one point using a quantitative approach.

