**3.6.4.4. Measurements, procedures and analysis**

The following measurements will be done: demographic and environmental factors, anthropometrics, dietary intakes and patterns, and biochemical data. Same parameters and procedures, which were done at the baseline and described in section 3.6.2.4, will be followed. Data will be analysed using same procedures as described for baseline, with addition regression and ANOVA to measure changes from baseline to post intervention, and between experimental and control. See table 3.5 below. This is done to determine the changes in nutritional status that is likely to have occurred because of the intervention. A statistician will be consulted.

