**Table 3.5: Proposed data analysis table**

| **Descriptive Statistics** | **Categorical data** | **Numerical data** | |
| --- | --- | --- | --- |
|  |  | **Normally distributed** | **Non-normally distributed** |
| ***Socio demographic information***   - Age - Gender   ***Anthropometric measures***   - Weight, height, MUAC - Categorization according to Z-scores: height for age, weight for age and BMI for age   ***Nutrient intake from 24hr recall***   - Total intake, - Consumption pattern   ***Dietary patterns***  Frequency of inclusion of food item in the FFQ  Morbidity diary  **Biochemical measures**   - Serum zinc - haemoglobin - Serum Ferritin - C-reactive protein - Transferrin saturation - Serum ferritin | Frequencies n (%) | Mean $\pm$ SD | Median and IQR |
| ***Analytical statistics-*** |  |  |  |
| ***Comparison of micronutrient status by subject characteristics*** | Pearson’s Chi-square test/Fishers exact test | ANOVA/T-test | Kruskal-Wallis/Mann-Whitney U tests |
| ***Association between dietary intakes and micronutrient status*** | Regression analyses with dietary intakes and anthropometric indices as dependent variables and all other as independent | | |
| ***Validation of dietary intake and micronutrient status against the intervention*** | Spearman’s correlation coefficient  Comparison of means/means Weighted kappa statistic for agreement testing  Bland Altman plots for bias and agreement testing | | |

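### The CRP cut-off in the iron table cannot be applied, and as written ferritin and zinc are read without reference to inflammation

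*Protocol*

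**What the plan says.** The primary aim (section 2.3) is to improve zinc and iron status, so ferritin and serum zinc are central outcomes.

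- **Role of CRP.** The baseline objectives (section 3.6.2.2) read "To determine the iron status of pre-school children using hemoglobin, serum ferritin, transferrin receptor and C- reactive protein (CRP"). CRP thus stands beside haemoglobin and ferritin as an iron-status measure. Section 3.6.2.5 and the post-trial objectives (section 3.6.4.2) repeat this.
- **Cut-offs.** The biochemical part of the data analysis section introduces its tables as the cut-off points to be used. The iron table is titled "An indication of lower cut-offs of serum iron concentration", in μg/L. Its ferritin row is "Serum ferritin | (SF) <12 μg/L" and its CRP row is "C-reactive protein | 1 and 2.9 mg/L". The zinc cut-offs (Table 3.2) vary by age, sex, time of day and fasting, not by CRP.
- **Timing.** Section 3.6.4.4 says of the post-trial survey: "Same parameters and procedures, which were done at the baseline and described in section 3.6.2.4, will be followed". The section it cites covers recruitment. The measurements are in 3.6.2.5, and the intent is clear. CRP is in the laboratory package budgeted for 436 children twice (Table 3.7).
- **Analysis.** Table 3.5 lists "C-reactive protein" among the biochemical measures to be described. Its regression row takes dietary intakes and anthropometric indices as outcomes. Section 3.6.4.4 adds regression and ANOVA for change and for the arm comparison, and names no covariates.

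**The concern.** CRP marks inflammation. It does not measure iron stores. Inflammation raises ferritin and lowers serum zinc, so CRP is collected alongside them to show when those values are unreliable. The protocol never says this. It gives CRP the role of an iron indicator and a cut-off that cannot be read.

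If the text is followed literally, an iron-deficient child who is inflamed can be counted as replete, and a zinc-replete child who is inflamed can be counted as deficient. The two outcomes are pushed in opposite directions. Preschools are randomised, six in section 3.4 and eight in the feeding-trial schematic, so there are three or four per arm. Illness concentrated in one or two preschools at the endline blood draw could therefore fall unevenly between arms. Section 2.5 also expects improvement from baseline within the intervention group. That comparison is exposed to any change in inflammation between visits, and the deworming dose given at baseline blood collection is one reason such a change could occur.

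Leaving the threshold open also means that it could be chosen after the data are seen.

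**Working it through.** **1. Can the CRP entry classify a child?** Take CRP values of 0.5, 2 and 20 mg/L and three possible readings of the entry:

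| Reading | 0.5 | 2 | 20 |
| --- | --- | --- | --- |
| Above 1 is abnormal | no | yes | yes |
| Above 2.9 is abnormal | no | no | yes |
| Between 1 and 2.9 is abnormal | no | yes | no |

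The readings flag different children. The table's title, which speaks of lower cut-offs, would suggest that low values are the abnormal ones, which is the wrong direction for an inflammation marker. Nothing in the text chooses between them.

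**2. Does a stated rule link CRP to ferritin or zinc?** The ferritin row has one value. The zinc table has no CRP column. Table 3.5 describes CRP, and its stated regressions have diet and anthropometry as outcomes, so CRP could at most be a predictor of those. Section 3.6.4.4 leaves covariates open. No rule is stated, and none is excluded.

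**3. Illustrative effect on prevalence.** The only figure from the documents is the earlier district result in section 1.5.1: "the prevalence of iron deficiency was 7.2% when using serum ferritin and even higher (28.1%) when with transferrin saturation". The rest is assumed: log-normal ferritin with log-SD s = 0.7, share inflamed q = 10% to 30%, and ferritin multiplied by f = 1.3 to 2.0 in inflamed children. The 7.2% is treated as uncorrected for inflammation, which is also an assumption. With p the true share below 12 μg/L and z(p) its normal quantile:

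observed share = (1 − q)·p + q·Φ(z(p) − ln f / s)

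Set this to 0.072 and solve for p. Example with q = 0.2 and f = 1.5: p = 8.37%, z(p) = −1.380, ln 1.5 / 0.7 = 0.579, Φ(−1.960) = 0.0250. Check: 0.8 × 0.0837 + 0.2 × 0.0250 = 0.072.

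| Share inflamed | f = 1.3 | f = 1.5 | f = 2.0 |
| --- | --- | --- | --- |
| 10% | 7.6% | 7.7% | 7.9% |
| 20% | 8.1% | 8.4% | 8.8% |
| 30% | 8.6% | 9.1% | 9.8% |

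True prevalence is 7.6% to 9.8%, which is 0.4 to 2.6 points above the observed figure, or about 2 to 11 children in 436. Among children who are both deficient and inflamed, the fixed cut-off misses about 53% to 90%. As a share of all deficient children this is 5% to 27%.

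**4. Illustrative effect on mean ferritin.** If the share inflamed differs by d between arms or visits, the ratio of geometric means shifts by exp(d·ln f) − 1.

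- d = 10 points: 2.7%, 4.1%, 7.2% for f = 1.3, 1.5, 2.0.
- d = 20 points: 5.4%, 8.4%, 14.9%.
- A fall of 20 points between visits: −5.1%, −7.8%, −12.9%.

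For chance imbalance between arms, assume a between-preschool SD of 5 to 15 points in the share inflamed. With k preschools per arm the SD of the arm difference is SD × √(2/k), which is 3.5 points (SD 5, k = 4) to 12.2 points (SD 15, k = 3). A 1.96-SD imbalance then shifts the ferritin ratio by about 2% to 18%.

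No zinc calculation was made, because the documents give no basis for the size of the fall in serum zinc.

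**The case against.** The strongest reply is that CRP adjustment is the kind of detail a protocol leaves to its SAP. Table 3.5 is headed as proposed, a statistician is to be consulted, and regression covariates are not fixed. This stands against any claim that CRP is shut out of the iron or zinc analysis. A reader might infer that from Table 3.5, but the use of CRP is unspecified, not excluded. The reply does not rescue the cut-off or the role given to CRP, both of which the protocol itself states.

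A reader might also infer that infection at six months goes unrecorded because the infection-free criterion applies at entry. The documents do not support that. The post-trial survey repeats the baseline procedures, which include CRP, a full blood count intended partly to detect infection, temperature, a 15-day illness history and a morbidity checklist. What is missing is a stated use for these data.

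The 53% to 90% figure is tempting but covers only children who are both deficient and inflamed. The gap between 7.2% by ferritin and 28.1% by transferrin saturation does not prove masking. Transferrin saturation also falls with inflammation, and the protocol does not say how the earlier study handled CRP.

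Finally, adjusting the main arm comparison for endline CRP has a real cost. Endline CRP is post-randomisation, and the protocol says that zinc supports immunity (section 1.4) and that deficiency increases infection (section 1.9). CRP may therefore lie on the treatment pathway. This objection stands and limits the remedy.

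**Conclusion.** The point holds in limited form and is moderate. The CRP entry is unusable as printed, CRP is given the wrong role, and the stated reading of ferritin and zinc makes no reference to it.

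The size of the consequence cannot be computed from the documents. Under the stated assumptions, 7.2% observed low ferritin corresponds to 7.6% to 9.8% true, a modest shift. Inflammation that is equal in both arms mainly misclassifies children and dilutes differences. It biases the arm comparison only if it differs by arm, which is plausible with three or four preschools each. It biases the baseline-to-endline comparison if it changes between visits. The protocol states no expected seed effect, so a shift of a few to about 15% in geometric-mean ferritin cannot be judged against a target.

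**What to change.** 1. In Table 3.3, replace the CRP entry with one pre-specified upper threshold that flags inflammation, and separate it from the lower cut-offs. The sponsor should choose the value with its laboratory before outcome data are seen.
2. In sections 3.6.2.2, 3.6.2.5 and 3.6.4.2, describe CRP as an inflammation marker used to interpret ferritin and zinc, not as an iron-status indicator.
3. Report ferritin-defined iron deficiency and serum zinc status at both visits, either separately below and above the threshold or after CRP correction.
4. Keep the arm comparison without endline CRP as the main analysis. Add, as a sensitivity analysis, the comparison of ln(ferritin) and of serum zinc adjusted for CRP, and state that endline CRP is post-randomisation and may lie on the treatment pathway.

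The cost is wording in two tables and three sections, plus a second set of results to report. No new samples or assays are needed, because CRP is already budgeted for both visits.
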